## 3. Study design

This study is designed to compare the accuracy and usefulness of breast cancer screening of women aged 40-49 between two groups, i.e., the intervention group screened with a combination of mammography and ultrasonography and the non-intervention group screened with mammography. To this end, the below shown two groups are incorporated into this study, with individuals or clusters serving as units.

- (1) Ultrasonography combined group (mammography + ultrasonography or mammography + clinical breast examination + ultrasonography)
- (2) Ultrasonography uncombined group (mammography alone, or mammography + clinical breast examination)

The targeted number of subjects is 60,000 for each group (120,000 subjects in

total). Of these subjects, 50,000 subjects from each group will receive two sessions of breast cancer screening at an interval of 2 years.

The targeted number of subjects was set on the basis of the forecast as to the capability of elevating the sensitivity (the primary endpoint) by the use of ultrasonography in combination with conventional mammography.

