## 2.5 Sample size

### Primary endpoints:

The primary endpoints are defined as differences in sensitivity/ specificity and a detection rate of the first breast cancer screening between the intervention group and non-intervention group as previously mentioned. The sample size was calculated based on a previous study comparing sensitivity between screening with CBE alone and mammography in combination with CBE.

In this study that was used for understanding interval cancer (cancer identified in screened individuals without abnormality during a period between the screening and the next screening) in population-based cancer registry data in Miyagi Prefecture, the sensitivity of breast cancer screening using mammography in combination with CBE was superior to that of CBE alone in all age groups. However, the sensitivity was 71.4% for the age of 40 to 49 years, 85.8% for the age of 50 to 59 years, and 87.2% for the age of 60 to 69 years; thus, it was lowest for the 40's. Of 20,587 subjects aged 40 to 49 years, breast cancer occurred in 63 subjects during two years after screening including screen-detected breast cancer. Of these, screen-detected breast cancer was in 45 subjects, and interval cancer was in 18 subjects (sensitivity:  $45/63 = 71.4\%$ ).

Furthermore, assuming that a combination with ultrasonography would increase the number of subjects with screen-detected cancer and that the incidence of interval cancer would be decreased by half (decrease from 18 to 9

subjects), sensitivity in the ultrasonography combined group would be 86% (54/63). A total of 130 subjects with breast cancer would be necessary for demonstrating this increase in sensitivity with a two-sided significance level of 5% at a power of 80%. When it was converted to the number of subjects undergoing screening, a sample size of 42,500 subjects per group was estimated.

Secondary endpoint:

The secondary endpoint is defined as difference in the cumulative incidence rate of advanced breast cancer during the follow-up period between the intervention and non-intervention groups as previously mentioned. As with the primary endpoints, the sample size was calculated based on the previous study comparing sensitivity between screening with CBE alone and mammography in combination with CBE.

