|                                                                    | 2007                     | 2008                      | 2009                      | 2010                      | 2011                      | 2012                     |
|--------------------------------------------------------------------|--------------------------|---------------------------|---------------------------|---------------------------|---------------------------|--------------------------|
| Intervention group                                                 | A1
(5000
subjects) | A2
(15000
subjects) | A1
(5000
subjects)  | A2
(15000
subjects) |                           |                          |
|                                                                    |                          |                           | A3
(15000
subjects) | A4
(5000
subjects)  | A3
(15000
subjects) | A4
(5000
subjects) |
| Non-intervention
group                                          | B1
(5000
subjects) | B2
(15000
subjects) | B1
(5000
subjects)  | B2
(15000
subjects) |                           |                          |
|                                                                    |                          |                           | B3
(15000
subjects) | B4
(5000
subjects)  | B3
(15000
subjects) | B4
(5000
subjects) |
| Cumulative No. of
subjects newly
enrolled                    | 10000
subjects        | 40000
subjects         | 70000
subjects         | 80000
subjects         |                           |                          |
| Cumulative No. of
subjects undergone
the second
screening |                          |                           | 10000
subjects         | 40000
subjects         | 70000
subjects         | 80000
subjects        |
| No. of subjects
screened each year                              | 10000
subjects        | 30000
subjects         | 40000
subjects         | 40000
subjects         | 30000
subjects         | 10000
subjects        |

163 A1, B1: enrolled in 2007, and re-screened in 2009.

164 A2, B2: enrolled in 2008, and re-screened in 2010.

165 A3, B3: enrolled in 2009, and re-screened in 2011.

166 A4, B4: enrolled in 2010, and re-screened in 2012.

167

168 3.2 Secondary endpoint

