#### 5.5 Breast density classification

In this study, we used cases enrolled from the screening center in Miyagi prefectures, as we could examine and confirm the breast density. Mammography density measure was evaluated depending on the fifth edition of Breast Imaging Reporting and Data System (BI-RADS), visual judgment data were classified as follows: (a) almost entirely fatty; (b) scattered areas of fibro-glandular density; (c) heterogeneously dense, which may obscure detection of small masses; and (d) extremely dense, which lowers the sensitivity of mammography screening.

Three expert physicians reevaluated mammographic density of the first screening. No personal identifiers were contained in the digital mammograms. All information of screening results, medical check and follow up data were blinded.

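### The SAP's sample size calculation needs 42,500 women per group for 80% power, but its schedule enrols 40,000 (about 78% before exclusions and clustering) and the protocol plans 60,000

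*Combined protocol and SAP*

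**What the plan says.** SAP 2.5 takes its control sensitivity from a regional registry study of 20,587 women aged 40 to 49, in which "screen-detected breast cancer was in 45 subjects, and interval cancer was in 18 subjects", so 45/63 = 71.4%. Halving the interval cancers gives 54/63, printed as 86%. It then says that "A total of 130 subjects with breast cancer would be necessary" to show this increase "with a two-sided significance level of 5% at a power of 80" per cent, and that after conversion to women screened "a sample size of 42,500 subjects per group was estimated". Protocol section 3 has the same calculation and calls 42,500 per group the minimum.

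Three sizes follow from that one calculation:

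- SAP 3.1 lists four cohorts per group of 5,000, 15,000, 15,000 and 5,000. All are screened a second time; for example, "A3, B3: enrolled in 2009, and re-screened in 2011". The cumulative row ends at 80,000 newly enrolled women for both groups together.
- Protocol section 3 states: "The targeted number of subjects is 60,000 for each group", with 50,000 per group screened twice. It considers 50,000 per group enough for the sensitivity analysis.
- Protocol section 7 lists three cohorts per group of 15,000, 35,000 and 10,000. The third is not scheduled for a second screen.

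SAP 6.3 removes non-randomised, ineligible, withdrawn and double-entered women and those without first-screening data. SAP 7.2.1 also removes women of unknown cancer status from the sensitivity and specificity analyses. SAP 6.2 and 7.2.2 pool individually and cluster-randomised women using GEE with a robust variance. SAP 2.5 contains neither a loss rate nor a design effect.

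**The concern.** A reader who takes the SAP alone finds a required number and, in the next section, a planned number 2,500 per group (5.9%) below it, without comment. A reader who compares it with the protocol finds a different target, different cohorts and a different set of women invited back. SAP section 11, on changes to planned analyses, records only the exclusion of non-randomised women.

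The calculation also treats every scheduled woman as analysed and independent, while the analysis sections assume neither. At stake is whether the 80% stated for sensitivity, the endpoint on which the trial was sized, describes the trial the SAP schedules, and which trial size is in force.

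**Working it through.** **Inputs from the documents.** Control sensitivity p1 = 45/63 = 0.7143; intervention sensitivity p2 = 54/63 = 0.8571; two-sided 5%; power 80%; two-year cancer rate 63/20,587 = 0.306% (SAP 2.5). 40,000 per group (SAP 3.1). 50,000 and 60,000 per group (protocol section 3). 42 organizations (SAP 2.2).

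**Step 1: reproduce the plan's figure.** The plan does not name its method. The usual two-proportion formula with pooled variance under the null and no continuity correction is

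n = [1.960 × √(2p̄(1 − p̄)) + 0.842 × √(p1(1 − p1) + p2(1 − p2))]² / (p2 − p1)², with p̄ = 99/126 = 0.7857.

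This gives (1.960 × 0.5803 + 0.842 × 0.5714)² / 0.1429² ≈ 128.3, so 129 cancers per group against the stated 130. Conversion: 130 × 20,587/63 = 42,481, against the stated 42,500. Both figures reproduce, and 130 is the number for each group.

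**Step 2: power at the scheduled sizes.** Expected cancers per group are e = N × 63/20,587, and

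power = Φ{[(p2 − p1) − 1.960 × √(2p̄(1 − p̄)/e)] / √[(p1(1 − p1) + p2(1 − p2))/e]}.

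For N = 40,000, e = 122.4 and power = Φ[(0.1429 − 0.1028)/0.0516] = Φ(0.776) = 78.1%.

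| Women per group | Source | Cancers per group | Power |
|---|---|---|---|
| 42,500 | SAP 2.5 | 130.1 | 80.5% |
| 40,000 | SAP 3.1 | 122.4 | 78.1% |
| 50,000 | Protocol 3, screened twice | 153.0 | 86.5% |
| 60,000 | Protocol 3, target | 183.6 | 91.9% |

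With the rounded 71.4% and 86% in place of the fractions, power at 40,000 is 80.0%. Those rounded inputs would require 123 cancers per group rather than 130, so the fractions match the plan's own number better. An exact enumeration of the chi-square test with 122 cancers per group gives 78.9%, so the approximation is not driving the result.

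**Step 3: exclusions and clustering, illustration only.** Effective cancers = 40,000 × (1 − loss) × (63/20,587) / design effect. The loss rates and design effects below are assumptions; the documents give none.

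| Cancers lost | Design effect | Effective cancers per group | Power |
|---|---|---|---|
| 5% | 1.0 | 116.3 | 76.0% |
| 10% | 1.0 | 110.2 | 73.7% |
| 0% | 1.1 | 111.3 | 74.1% |
| 10% | 1.1 | 100.2 | 69.6% |

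On the scale of the design effect: 80,000 × 63/20,587 = 245 cancers, and 245/42 ≈ 5.8 per organization. If the organization were the cluster, an assumed intracluster correlation of 0.02 gives 1 + (5.8 − 1) × 0.02 ≈ 1.10.

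For comparison, 50,000 per group with 5% lost and a design effect of 1.1 still gives 81.2%.

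**The case against.** The strongest reply is that the documented shortfall is small and the rest is conjecture. The schedule alone costs about 2 points, or nothing with the printed 86%. Every larger loss needs a rate or correlation that the documents do not supply. Losing women is not the same as losing cancers, because SAP 5.2 also finds cases through hospital records and registries. Women randomised individually within a site do not carry the same cluster inflation. A cancer rate of 130/40,000 = 0.325% instead of 0.306% would restore the 130. Protocol section 18 says the primary analysis has been reported with significantly higher sensitivity in the intervention group, so low power can no longer cause a missed primary result.

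Most of this stands. It limits the size of the problem and is why no single reduced power figure can be asserted. It does not remove the mismatch between 40,000, 42,500 and 60,000, or the lack of any allowance in SAP 2.5. The protocol's 50,000 to 60,000 is 18% to 41% above 42,500 and could absorb losses and clustering; the SAP schedule keeps none of that margin.

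Three stronger readings might be inferred, and the documents support none of them:

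- A reader might take the total of 130 as 65 per group, which would leave the trial badly underpowered. The conversion to 42,500 per group that follows rules this out. SAP 2.5 also uses the same phrasing for its other sizes, which are explicitly per group.
- A reader might infer that the power depends on all 80,000 women returning. The primary endpoints concern the first screening (SAP 2.4.1), and SAP 5.2.2 accepts questionnaire or detailed-examination data in place of a second screen.
- A reader might apply 42,500 and 80% to the breast density analyses, for which SAP 5.5 says "we used cases enrolled from the screening center in Miyagi prefectures". Nothing in SAP 2.5 makes that claim.

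**Conclusion.** The point holds as an internal inconsistency with a modest, partly unquantifiable effect on power. On the SAP's own inputs and schedule, about 122 cancers per group are expected and power is about 78% (80% with the rounded 86%) before any exclusion or clustering. With net loss of cancers or positive within-cluster correlation, and the cancer rate as assumed, it is lower. The documents do not say by how much. The 70 to 76% illustrations rest on assumed losses of 5 to 10% and a design effect of 1.0 to 1.1.

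A reader might conclude that the trial as run was seriously underpowered. That does not follow: the protocol sizes give 86% to 92% before losses, and the documents do not establish loss rates or correlations large enough to support that conclusion. The text should be corrected because it is the sample size justification for the primary endpoint, but the matter ranks below an essential correction.

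**What to change.** 1. Reconcile the SAP 3.1 schedule with protocol sections 3 and 7: size per group, cohorts, and which cohorts are screened again. State which is in force and why it changed.
2. In SAP 2.5, write 130 cancers per group (260 in total).
3. Keep 42,500 per group and 80% as the design-stage calculation. Beside it, give the power at the size actually planned, with the expected evaluable cancers per group, the loss rate and the design effect each stated as a labelled assumption. At 40,000 per group the starting point is 122 cancers and 78%.

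The cost is a few lines of SAP text and a short recalculation, with no additional enrolment. The only downside is a slightly less favourable power statement.

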## 5.2 Rules for determining the presence or absence of breast cancer

Breast cancers were ascertained by diagnostic assessment of first and second screening results, hospital discharge records and cancer registry databases. Miyagi prefecture has a sophisticated system of local registration for cancer, which contains virtually all breast cancer patients' registration conducted in Miyagi prefecture. Therefore, it was possible to identify screening-detected cancer, interval cancers and not breast cancer exactly. The latest date for the censoring of data on breast cancer for the purpose of analysis will till February 2020.

### 5.2.1 Had Breast Cancer (cancer detected at the first screening, interval cancer)

Based on the above-mentioned definitions of screening intervals, cancer detected at the first screening, and interval cancer, subjects classified into (1) FN, (3) FN, (5) TP or (7) TP in the green frame will be used for calculating sensitivity of the first screening.

### 5.2.2 Did not have Breast Cancer (not breast cancer)

Subjects without breast cancer will be defined as those who do not meet the abovementioned Had Breast Cancer and meet any of the following criteria:

- Data at the second screening are inputted, and no breast cancer is reported.
- Questionnaire data are inputted, and no breast cancer is reported.
- Data at the second screening are missing (screening and questionnaire), but during an interval between the first to second screening, at least one detailed examination is performed, and the results of the detailed examination revealed no breast cancer.
- Subjects with a diagnosis of breast cancer after the screening interval specified in this study: Subjects who meet (2) TN, (4) TN, (6) FP or (8) FP outside the green frame.

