#### 16.1. Institutional data center

(1) Invites subjects to this study (white advising people to receive breast cancer screening);

(2) Checks the eligibility of candidate subjects at the screening site and explains the objectives of this study to eligible individuals, followed by collection of informed consent to the study in writing;

(3) Conducts screening with the assigned method and reports the results to participants;

(4) Advises subjects rated as requiring detailed examination to receive the examination and checks the detailed test results;

(5) Stores documents (consent form, screening results, detailed test results);

(6) Enter data of subjects (information for subject identification, background information, screening results and detailed test results) and send them to the Central Data Center;

(7) Receives a consent cancellation form and stores it, followed by reporting to the Central Data Center;

(8) Conducts precision control of screening. To this end, periodically checks the maintenance/inspection history of devices, methods of test, etc., referring to the study protocol and the manual, and reports the results of check to the Central Data Center periodically (four times a year). Cooperate with sampling test for evaluation of mammograms and ultrasound images;

(9) Advises the subjects receiving the first breast cancer screening in latter half of 2007 to 2008 (Group A1, A2, B1 and B2 mentioned below) to receive the second screening 2 years after the first screening. At that time, the presence/absence of breast cancer detected after the first screening is checked (refer to “8.5. Follow-up” and “9. Follow-up methods” for details).

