## 2.4 Endpoints

### 2.4.1 Primary endpoints

Differences in sensitivity/ specificity and a detection rate of the first breast cancer screening between the intervention group and non-intervention group.

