### 5.2.3 Had unknown status (unknown)

Subjects who do not fall into either of the above Items 1) Had Breast Cancer or 2) Did not have Breast Cancer will be defined as Had unknown status. Subjects whose medical examination data in a report of breast cancer are not grasped will be classified into unknown.

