|--------------------------------------------|--------------------------------------------------------------------------------------------------------------|------------------------------------------------------------------------------|
| Detection rate of screening, %
(95% CI) | The number of cancers with a positive initial interpretation among 1,000 screening examinations.             |                                                                              |
| Sensitivity, %
(95% CI)                 | $\text{Sensitivity} = \frac{[5]\text{TP}+[7]\text{TP}}{[5]\text{TP}+[7]\text{TP}+[1]\text{FN}+[3]\text{FN}}$ | (Number of true positive assessments) / (Number of all positive assessments) |
| Specificity, %
(95% CI)                 | $\text{Specificity} = \frac{\text{TN}}{\text{TN}+\text{FP}}$                                                 | (Number of true negative assessments) / (Number of all negative assessments) |

365 The 95% CIs will be calculated using the binomial distribution method.

366 At the statistical analysis/ data monitoring committee meeting held on October 28, 2013, consensus was reached  
 367 that subjects having an unknown status would be excluded from the analyses of sensitivity and specificity.

368 7.2.2 Method of the primary analysis taking account of correlations within the cluster

369 All “screen-detected cancer,” “interval cancer” and “subjects without cancer” at the first screening to be used for  
 370 calculating sensitivity/ specificity, the primary endpoints, are binary outcomes. As an analysis method for  
 371 estimating the primary endpoints in the two groups, GEE taking account of correlations within the cluster will be  
 372 used. For estimation of the parameters, robust variance estimator with a compound symmetry structure as a  
 373 working correlation matrix will be employed.

374

375     **8. Statistical Analysis Rules**

| Item                                                                         |                                  | Display digit                                                                                                                                                                                                                                               |

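### Entry to the specificity denominator depends on having had a work-up: unfollowed women with a negative detailed examination are kept, unfollowed women without one are excluded

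*Combined protocol and SAP*

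**What the plan says.** SAP 2.4.1 makes specificity part of the primary endpoints: "Differences in sensitivity/ specificity and a detection rate of the first breast cancer screening between the intervention group and non-intervention group". SAP 7.2.1 computes it as TN/(TN+FP) among women classed as not having breast cancer.

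Three rules decide who is in that denominator.

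- SAP 5.2.2 gives four routes to the cancer-free class. The first two are a second screen, or a questionnaire, with no cancer reported. The third covers women who have neither. It accepts them if, between the two screens, "at least one detailed examination is performed, and the results of the detailed examination revealed no breast cancer". The fourth covers cancers diagnosed after the screening interval.
- SAP 5.2.3 defines the unknown class by exclusion: "Subjects who do not fall into either of the above Items 1) Had Breast Cancer or 2) Did not have Breast Cancer".
- SAP 7.2.1 records the consensus of 28 October 2013 "that subjects having an unknown status would be excluded from the analyses of sensitivity and specificity".

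Two other places bear on the point. Protocol 16.1 shows who is sent for work-up; the institutional data center "Advises subjects rated as requiring detailed examination to receive the examination and checks the detailed test results". SAP 5.2, after describing the Miyagi cancer registry, says: "Therefore, it was possible to identify screening-detected cancer, interval cancers and not breast cancer exactly". The list in 5.2.2 has no registry-negative route. No sensitivity analysis for unknown women is planned.

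**The concern.** Take two women who both miss the second screen and return no questionnaire. One was recalled at the first screen and had a negative work-up; she stays in as a false positive. The other was not recalled and had no work-up; she would have been a true negative, but she is unknown and is dropped. Retention therefore depends largely on the result of the test being evaluated, which is a form of partial-verification bias.

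The effect need not cancel between arms. Protocol 6.1 sends a woman in the ultrasonography arm for work-up if either test is Category 3 or higher, so that arm should have more false positives to retain. At stake is the estimated specificity in each arm and the estimated loss of specificity from adding ultrasonography.

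**Working it through.** **What the plan supplies.** It states no expected specificity, recall rate, work-up uptake or follow-up rate, so there is no planned specificity figure to reproduce. Two of its figures are useful. Interval cancers in the reference cohort were 18 of 20,587 women, or 0.09% (protocol 3, SAP 2.5). The planning size is 42,500 per group, which follows from 130 × 20,587/63 = 42,481.

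**Notation.**

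- q: true false-positive fraction (1 − specificity)
- a0, a1: fraction of non-recalled and of recalled women with a second screen or questionnaire
- w: fraction of recalled women with a completed negative work-up

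**Formula under the SAP rule**, treating all work-ups as being in recalled women:

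Sp = (1−q)·a0 / {(1−q)·a0 + q·[a1 + (1−a1)·w]}

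With k = [a1 + (1−a1)·w]/a0, the bias is −q(1−q)(k−1)/[1 + q(k−1)]. It is zero at k = 1 and negative when k > 1.

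**Case 1: follow-up the same by recall status and arm (a0 = a1 = a).** Assumed: w = 0.9; q = 8% control and 12% ultrasonography; true difference −4.0 points. For example, at a = 0.90 in control, TN = 0.92 × 0.90 = 0.828 and FP = 0.08 × (0.90 + 0.10 × 0.90) = 0.0792, so Sp = 0.828/0.9072 = 91.27%.

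| a | Control Sp (bias, points) | Ultrasonography Sp (bias, points) | Change in difference |
|---|---|---|---|
| 0.80 | 90.37% (−1.63) | 85.69% (−2.31) | −0.69 |
| 0.90 | 91.27% (−0.73) | 86.96% (−1.04) | −0.31 |
| 0.95 | 91.65% (−0.35) | 87.50% (−0.50) | −0.15 |
| 0.99 | 91.93% (−0.07) | 87.90% (−0.10) | −0.03 |
| 1.00 | 92.00% (0) | 88.00% (0) | 0 |

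With q = 9% and 12% instead (true difference −3.0), the estimated difference is −3.2 at a = 0.90 and −3.5 at a = 0.80 (89.2% against 85.7%). Over a wider grid (q = 5/8%, 8/12% and 10/15%; w = 0.6 to 1.0; a = 0.80 to 1.00), the extra bias in the ultrasonography arm runs from 0 to 0.88 points, and the largest per-arm bias at a = 0.99 is 0.13 points.

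For scale, the binomial standard error of the difference at 42,500 per group, ignoring clustering, is √(0.08×0.92/42,500 + 0.12×0.88/42,500) = 0.21 points. It would be larger in the Miyagi subset that SAP 5.5 uses.

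**Case 2: follow-up differs by recall status.** With a0 = 0.90 and a1 = 0.70, k = 1 when w = (0.90 − 0.70)/(1 − 0.70) = 0.67. Below that uptake the bias is upward: at w = 0.5 and q = 8% it is +0.41 points.

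**Case 3: follow-up differs by arm.** With w = 0.9, control at a = 0.90 has bias −0.73. Ultrasonography at a = 0.93 has −0.71, so the arm ordering is gone.

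**Case 4: what deleting the third criterion would do.** Keep a0 = 0.90, a1 = 0.70, w = 0.9 and q = 8%/12%.

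- SAP rule: 0.828/(0.828 + 0.0776) = 91.43% and 0.792/(0.792 + 0.1164) = 87.19%; difference −4.2.
- Criterion deleted: 0.828/(0.828 + 0.056) = 93.67% and 0.792/(0.792 + 0.084) = 90.41%; difference −3.3.
- Truth: −4.0. Deletion is further off than the rule it replaces.

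**Counting unknowns as cancer-free.** All women with a first-screen result are then kept, so k = 1 in every case above. The error left is undetected cancer among the unknowns. If they resemble the reference cohort, interval cancers are 0.09% of them. Using all 63 cancers, 63/20,587 = 0.31%; with 20% unknown that is 0.20 × 0.31% = 0.06% of women.

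**The case against.** The strongest reply is that the size, and even the sign, rest on assumptions. That stands. A reader might infer from the rules alone that specificity is understated and the harm of ultrasonography overstated. The documents do not support that as a fact: Cases 2 and 3 show that the direction or the arm ordering changes with plausible differences in follow-up, and no follow-up rates are given. Missing follow-up may also be small. Protocol 9 has non-attenders telephoned, protocol 16.2 lets the Central Data Center contact women directly, and SAP 3.1 plans a second screen for all 80,000. Protocol 3 plans one for 50,000 of 60,000 per group; neither is an observed rate.

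A second reply is that SAP 5.2 reports exact identification of non-cancer in Miyagi, the source of women for the density analysis. If registry status was applied to all of them, the bias disappears. A reader might conclude instead that unknown women are dropped needlessly, but that assumes 5.2.2 overrides 5.2. The text shows only that the two sections have not been joined.

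Third, the split is by work-up and not strictly by recall. A non-recalled woman with a negative symptomatic work-up also meets the third criterion, and a recalled woman with neither work-up nor follow-up is also unknown. This blurs the asymmetry but does not remove it.

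Finally, nothing shows that a conclusion would change. There is no margin or decision rule for specificity, the sample size rests on sensitivity, and in Case 1 the difference keeps its sign.

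**Conclusion.** The defect is in the rules: with incomplete follow-up, inclusion in a primary-endpoint denominator depends on whether a woman had a work-up, and so largely on her first-screen result. No planned analysis shows how much this matters.

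If follow-up is similar by recall status and arm, specificity is expected to be biased down, and more in the ultrasonography arm. With 10–20% missing follow-up, 90% work-up uptake and false-positive fractions of 8–9% in control and 12% with ultrasonography (all assumed), the bias is roughly 0.7–2.3 points per arm and 0.2–0.7 points in the difference. At 1% missing it is about 0.1 point or less per arm. Under other follow-up patterns the sign or the ordering may change.

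This is a should-fix. A reader might take it as invalidating the specificity comparison, or as a reason to strike the third criterion; neither follows.

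**What to change.** 1. Do not simply delete the third criterion of SAP 5.2.2.
2. Add a specificity analysis on all ITT women with a first-screen result and no ascertained breast cancer. Unknown women count as cancer-free and enter as true negatives or false positives by first-screen category. Report it beside the current complete-follow-up analysis. Protocol 18 says the primary analysis has already been reported, so label it as an added analysis.
3. Tabulate unknown women by arm and recall status, so that readers can see the follow-up fractions on which the direction depends.
4. Reconcile SAP 5.2 with 5.2.2 and 5.2.3. Where registry linkage exists, as in Miyagi, add absence of breast cancer in the registry at 24 months as a criterion for every woman, whatever her first-screen category.

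Cost: SAP wording and a small re-run; item 2 uses data already held. About 0.1% of women or fewer may be wrongly counted as cancer-free. Item 4 is limited to linked areas, because protocol 5 only prefers sites with a precise registry and protocol 8.5 requires an application for each linkage.
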